# The BETTER WISE protocol: building on existing tools to improve cancer and chronic disease prevention and screening in primary care for wellness of cancer survivors and patients – a cluster randomized controlled trial embedded in a mixed methods design

**DOI:** 10.1186/s12885-018-4839-y

**Published:** 2018-09-26

**Keywords:** Cancer survivors, Chronic disease, Clinical practice guidelines, Prevention, Primary care, Screening

## Abstract

**Background:**

There is a pressing need to reduce the burden of chronic disease and improve healthcare system sustainability through improved cancer and chronic disease prevention and screening (CCDPS) in primary care. We aim to create an integrated approach that addresses the needs of the general population and the special concerns of cancer survivors. Building on previous research, we will develop, implement, and test the effectiveness of an approach that proactively targets patients to attend an individualized CCDPS intervention delivered by a Prevention Practitioner (PP). The objective is to determine if patients randomized to receive an individualized PP visit (vs standard care) have improved cancer surveillance and CCDPS outcomes. Implementation frameworks will help identify and address facilitators and barriers to the approach and inform future dissemination and uptake.

**Methods/design:**

The BETTER WISE project is a pragmatic two-arm cluster randomized controlled trial embedded in a mixed methods design, including a qualitative evaluation and an economic assessment. The intervention, informed by the expanded chronic care model and previous research, will be refined by engaging researchers, practitioners, policy makers, and patients. The BETTER WISE tool kit includes blended care pathways for cancer survivors (breast, colorectal, prostate) and CCDPS including lifestyle risk factors and screening for poverty. Patients aged 40–65, including both cancer survivors and general population patients, will be randomized at the physician level to an intervention group or to a wait-list control group. Once the intervention is completed, patients randomized to wait-list control will be invited to receive a prevention visit. The main outcome, calculated at 12-months follow-up, will be an individual patient-level summary composite index, defined as the proportion of CCDPS actions achieved relative to those for which the patient was eligible at baseline. A qualitative evaluation will capture information related to program outcome, implementation (facilitators and barriers), and sustainability. An economic assessment will examine the projected cost-benefit impact of investing in the BETTER WISE approach.

**Discussion:**

This project builds on existing work and engages end users throughout the process to develop, implement, and determine the effectiveness of a multi-faceted intervention that addresses CCDPS and cancer survivorship in primary care settings.

**Trial registration:**

ISRCTN21333761. Registered on December 19, 2016

## Background

Research suggests that primary care is the ideal setting for cancer surveillance [1–3] and cancer and chronic disease prevention and screening (CCDPS) [4–6]. Reducing risk factors and detecting cancer early through evidence-based CCDPS activities is important for continued sustainability of our healthcare system [7–9]. Unfortunately, a substantial gap remains between CCDPS recommendations and actual practice [10–13]. The Building on Existing Tools to Improve Chronic Disease Prevention and Screening in Primary Care (BETTER) trial found that, on average, nine out of 28 CCDPS impactful actions were not being applied in practice [10]. The care gap is even larger for cancer survivors [14]. Despite numerous evidence-based actions and strategies that target CCDPS in primary care and are supported by clinical practice guidelines [10, 15], there are major barriers to translating this evidence into practice. For example, applying the US Preventive Service Task Force recommendations in practice was estimated to add an additional 7.4 h to a primary care physician’s day [11]. In addition to a lack of physician time, other barriers include unclear or conflicting guidelines [12, 13] and lack of enabling systems to apply these recommendations [11]. Presently, most guidelines focus on one specific cancer, medical condition, or a single risk factor [13, 16]. However, primary care providers (PCPs) need approaches that harmonize guideline recommendations across multiple conditions [13, 17].

The BETTER pragmatic cluster randomized controlled trial (RCT) demonstrated an effective CCDPS intervention in urban primary care settings [10]. The intervention utilized harmonized guidelines to address lifestyle risks through the introduction of a new role in the practice setting, the Prevention Practitioner (PP) [10, 18]. The PPs (e.g., LPN, RN, NP, dietitian) were trained on the evidence-based BETTER tool kit and obtained enhanced skills in CCDPS. They then assessed each patient’s CCDPS status based on medical records and patient self-report and met with patients one-on-one to build tailored prevention prescriptions through shared decision-making principles and motivational interviewing.

The BETTER intervention evaluated patient level outcomes using a composite index [19] of 28 evidence-based CCDPS actions (e.g., completed mammogram, measured blood pressure). The ratio of met actions to eligible actions (M/E) was 23.1% for patients receiving no intervention, and 55.6% for patients in the patient-level PP intervention arm [10].

The BETTER WISE project will build on this research by including a screen for poverty and adding a comprehensive follow-up approach for breast, colorectal, and prostate cancer survivors. Our objective is to determine whether the intervention achieves more CCDPS actions than standard care at 12 months following the initial prevention visit. We also aim to understand, if effective, how to best implement the approach into practice.

## Methods/design

### Study design

The BETTER WISE project adopts a mixed methods approach including a pragmatic two-arm cluster randomized controlled trial, and a quantitative and qualitative evaluation of the impact and implementation of the intervention.

### Research questions

Specific research aims, and questions are:To evaluate the BETTER WISE intervention consisting of a PP (a new skilled role in primary care practice for cancer survivorship and CCDPS) and the BETTER WISE tool kit:Is the BETTER WISE intervention effective?When used in diverse settings, does the approach improve individual patients’ cancer survivor surveillance and CCDPS targets, including reduced behavioural risks, as compared to usual care?To learn about the implementation of the BETTER WISE approach:Is implementation in diverse primary care settings feasible?What are the facilitators and barriers to uptake of the BETTER WISE approach?If effective, how can it be sustained? What modifications are required to scale and spread the approach and the PP role to diverse primary care settings?What is the near-term cost-benefit impact of investing in the BETTER WISE approach?

### Patient population

We target patients in the 40 to 65 age group as most cancer surveillance and chronic disease prevention and screening activities in primary care are applicable to this group [10].

### Cluster randomized controlled trial

#### Objective

The study aim is to determine if patients aged 40–65, including cancer survivors (breast, colorectal, and/or prostate) on routine survivorship care, randomized to receive an individualized prevention visit with a PP, have improved cancer surveillance and general prevention and screening outcomes as compared to standard care in a wait-list control group 12-months after the initial prevention visit.

#### Rationale for a pragmatic randomized controlled trial (RCT) design

Though the rigor of the RCT enhances internal validity, it risks limiting the external validity (i.e., generalizability) of the approach. The pragmatic design (minimal patient selection criteria, use of existing primary care practices, and tailoring of the intervention to the setting) enhances generalizability to other patients in diverse primary care practices. As such, the study will investigate the “real world” impact of the intervention. Generalizability will be enhanced by tailoring the intervention to the variable circumstances in the practices [20, 21]. The pragmatic RCT will allow us to conclude with confidence whether the intervention works over and above secular trends, something that is not achieved by a pre-vs-post-test design [22].

#### Randomization

A two-arm cluster RCT design will be used. The unit of randomization will be the physician, with participating physicians randomized to have their patients in the intervention group or wait-list control group. The physician is defined as the “cluster” to minimize the risk of contamination in that all patients in that physician cluster will either receive the intervention or wait-list control, according to the arm to which their physician was randomly assigned. Because participating physicians will be nested in a site, and some patients within a single clinical site will receive the intervention while others will not, there remains a risk of contamination. However, we perceive this risk to be low based on our BETTER trial experience [10]. Further, if contamination does occur, it would bias estimated effects towards the null hypothesis (i.e. there is no significant difference in outcomes between intervention and wait-list control groups).

#### Setting, recruitment, and sample

We will collaborate with physicians, primary care groups, and health organizations in three geographically disparate Canadian provinces--Alberta, Ontario, and Newfoundland & Labrador--to identify and invite urban, rural, and remote practices to participate in our project. We will conduct this trial in 16 primary care practices and recruit 64 physicians (32 in Alberta, 16 in Ontario, 16 in Newfoundland & Labrador). This approach will result in a total of 32 physicians allocated to the intervention group and 32 physicians to the wait-list control group (see design schemas Figs.1 and 2). Each practice will identify an individual within their setting to assume the role of the PP.

**Fig. 1 Fig1:**
[figure not shown]
BETTER WISE Project design schema for practices in Alberta

**Fig. 2 Fig2:**
[figure not shown]
BETTER WISE Project design schema for practices in Ontario and Newfoundland & Labrador

All eligible breast, colorectal, and/or prostate cancer survivors will be invited; the remainder of the sample will be designated as general population patients, which will include patients with complex needs. We plan to recruit 20 patients per physician (five cancer survivors and 15 general population patients), with priority given to cancer survivors.

#### Inclusion criteria

Eligible patients include those aged 40–65 for whom we have medical record access for the previous three years. Within this sample, we will target: 1) cancer survivors (breast, colorectal, prostate) on active surveillance for recurrence (i.e. are not palliative) and 2) general population patients (i.e., who do not have a history of breast, colorectal, or prostate cancer).

#### Exclusion criteria

Patients will be excluded if: 1) they are unable to give written informed consent, 2) we are unable to access their medical history for the previous three years, or 3) they are receiving active treatment for cancer. However, patients undergoing prophylactic or hormone treatments (e.g., aromatase inhibitors) will not be excluded.

#### Identifying the cancer survivor sample

The PPs and/or primary care clinic staff working with the research team will generate a list of eligible patients for each participating physician. Charts will be reviewed to confirm, based on pathology report results, that the patient is a cancer survivor.

#### Identifying the general population patient sample

The PPs and/or primary care clinic staff working with the research team will identify eligible patients from the remaining pool. To select patients in the non-cancer survivor sample, the study biostatistician will generate a random number sequence. Patients will be invited to participate in the order of the random number sequence and assigned a unique study identification (ID) number.

Standardized invitation letters will be signed by the PP and physician. As stated in the letter, the participating primary care site will call the patient five business days after mailing the invitation to determine if they are interested in participating. If the patient meets the inclusion criteria, a verbal consent process will be completed.

#### The intervention

The intervention consists of a one-hour prevention visit with the PP. Each practice setting will identify a clinician (e.g., LPN, RN, NP, dietitian) to take on the PP role and obtain skills in CCDPS and use of the BETTER WISE tools. The BETTER WISE tools were developed using the same process of evidence review and guideline harmonization as that used for the BETTER trial (Fig. 3) [13]. The tools received input from research, policy, and practice partners to ensure accurate and consistent CCDPS messaging. Guidelines, resources, and messages have been integrated into the BETTER WISE tool kit for CCDPS, providing a harmonized approach to prevention [8, 9, 14].

**Fig. 3 Fig3:**
[figure not shown]
Guideline harmonization and implementation plan for the BETTER trial. The triangle in the center of Fig. 82 is an extension of the ‘knowledge creation funnel’ in the knowledge to action cycle [13, 18, 39]. The knowledge synthesis is contextually integrated for each patient. The circumference refers to the steps for implementing the tools in both the practice- and patient-level interventions of the BETTER trial. Note: CVD = cardiovascular disease, EMR = electronic medical record

The BETTER WISE tools include: 1) the BETTER WISE health survey which includes information described in Table 1; 2) a poverty screening tool; 3) a diagram of the CCDPS targets to inform clinicians and assist with agenda setting when meeting with patients; 4) the CCDPS care maps including cancer (breast, colorectal, prostate) survivorship pathways to guide PP activities; and 5) a prevention prescription template to facilitate shared decision-making and collaborate with patients. The tools will be disseminated, published, and made available on the BETTER WISE website [23] and other websites to accelerate uptake.

**Table 1 Tab1:** The BETTER health survey

Description	Data to be Collected
General health status	depression, quality of life (e.g., EQ5D), lifestyle behaviours (tobacco and alcohol use, nutrition, and physical activity [29]), including readiness for change for each of these behaviours [30]
Demographic information	sex, gender, date of birth, citizenship, ethnic/cultural background, employment status, household income, level of education, and marital status
Family history	chronic diseases including, cancers, heart disease, and diabetes
Personal history	chronic diseases, including conditions to identify patients with complex needs (e.g., hypertension, diabetes mellitus, COPD, asthma, heart failure, ischemic heart disease, chronic renal failure, mental health, obesity, addiction)
Poverty screening	

Environmental scans with input from clinicians, PCPs, and PPs will identify national, regional, and local evidence-based tools and resources to integrate into the individual PP’s BETTER WISE tool kit [24].

The PP also receives training in Brief Action Planning based on the principles and practice of motivational interviewing [25, 26] which has demonstrated feasibility and effectiveness in lifestyle interventions [27]. Clinicians participating in BETTER WISE will learn a new collaborative model of care and new roles for physicians and PPs (see Figs. 4 and 5) [18].

**Fig. 4 Fig4:**
[figure not shown]
The Collaborative role of the Prevention Practitioner. CCDPS = cancer and chronic disease prevention and screening; PP = Prevention Practitioner

**Fig. 5 Fig5:**
[figure not shown]
The Prevention Practitioner role in detail. CCDPS = cancer and chronic disease prevention and screening; S.M.A.R.T = specific, measurable, attainable, realistic, time-based

##### Intervention group

Patients randomized to the intervention will be scheduled for a 60-min prevention visit with their PP. Patients will be asked to complete the BETTER WISE health survey prior to the visit and at six-month intervals up to 24 months after the initial visit (see Figs. 6 and 7). Intervention patients will also have the opportunity to review their written consent form online prior to beginning the health survey. Written consent will be obtained by the PP or another clinic staff member before the patient’s first prevention visit.

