##### Wait-list control group

Wait-list control patients will be mailed: 1) the website link to the BETTER WISE health survey, and 2) the study consent form to completed and returned to the study team using a pre-addressed, stamped envelope. Wait-list control patients will be asked to complete the health survey immediately after agreeing to participate in the study and before their first visit with the PP, which will be scheduled upon completion of the intervention period of the study approximately 12 months later. Additional screening and prevention data will also be obtained for wait-list control patients by the PP or primary care clinic staff from the patient’s medical chart during the same data collection periods.

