### Evaluation and impact of the intervention

#### Outcomes and statistical analysis

Outputs and outcomes include both practice- and patient-level outcomes (Fig. 8). To demonstrate the effectiveness of BETTER WISE, we will determine if cancer surveillance care and general prevention and screening outcomes improve for patients who receive an individualized visit with a PP, as determined by a composite index, when compared to wait-list controls at 12 months follow-up. The analysis will adhere to the intention-to-treat principle in that none of the enrolled patients will be excluded from analysis and all patients will be analyzed according to the randomization scheme (see Fig. 9). The unit of analysis will be the individual patient.

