##### Sample size calculations

Based on the findings from our previous research (BETTER trial and BETTER 2 study), we estimate the intra-class correlation coefficient (ICC) to be 0.30. From the BETTER trial, we anticipate the percentage of achieved CCDPS actions in the wait-list control arm will be approximately 20%. To detect a 20% intervention effect (i.e., the proportion of achieved CCDPS actions for patients randomized to the BETTER WISE intervention is 40%, compared to 20% for wait-list control) with 80% power, we will need to recruit approximately four patients per physician to achieve our sample size requirements per area of interest (cancer survivors and general population patients) at 5% alpha. The 20% intervention effect size is conservative given information gathered from the BETTER trial. As such, we would require four cancer survivors and four general population patients for each participating physician to have sufficient power to conduct sub-group analyses (i.e. measuring the effectiveness of the PP intervention in cancer survivors and the general population patients).

We will also target patients with complex medical needs as described by the province of Alberta’s billing definition of complex needs. In the BETTER trial, 25% of patients 40 to 65 years of age met the Alberta’s billing criteria for complex needs. To guarantee that we will recruit enough patients to meet the definition of complexity, we will increase our total sample size to 16 patients (four cancer survivors and 12 general population patients) for a total of four patients with complex needs (i.e., 25% of 16 = 4). This will allow sufficient power to conduct sub-group analyses with respect to measuring the effectiveness of the PP intervention on patients with complex needs.

To account for possible study withdrawal and/or loss to follow-up, we will further inflate our sample size by 25% for a total of 20 patients per physician (five cancer survivors and 15 general population patients) for a total sample size of 1280 patients (320 cancer survivors and 960 general population patients). A total of 30 patients per physician will be recruited to participate in the project to ensure our target sample size of 20 patients per physician is met. Participating practices may choose to over-sample cancer survivors or patients who meet the definition of complex needs in order to reach their target sample (five cancer survivors and 15 general population patients).

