**Fig. 10 Fig10:**
[figure not shown]
BETTER WISE Project timeline

Phase 2 of the project includes the pragmatic two-arm cluster RCT. The significant milestones are: 1) ethics approval obtained; 2) physicians and practices recruited, physicians randomized for RCT; 3) clinicians identified to take on role of PP and trained; 4) patients recruited; 5) completed PP visits with intervention and waitlist control patients.

Phase 3 of the project is the evaluation of impact.

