#### Research ethics considerations

Approvals from the relevant research ethics boards for participating sites in each of the three provinces will be obtained prior to the commencement of the trial. All patients in the research trial will provide written informed consent. Individuals who are not able to provide consent for reasons of language, literacy, or competency will be excluded. Since all elements of the patient-level intervention are consistent with best practice and could be offered as part of usual patient care by PCPs, there are no risks or harms associated with this approach.

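### Written consent is taken after physician randomization and by a different route in each arm, so the set analysed as intention-to-treat is formed by arm-specific filters

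*Protocol article*

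**What the plan says.** All places are in the protocol article.

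- **Unit and order.** Under *Randomization*: "The unit of randomization will be the physician". The Phase 2 milestones under *Timeline* read "2) physicians and practices recruited, physicians randomized for RCT; 3) clinicians identified to take on role of PP and trained; 4) patients recruited".
- **Common first step.** Under *Identifying the general population patient sample*, letters signed by the PP and the physician are followed by a telephone call and a verbal consent process. No distinction by arm is made.
- **Written consent, intervention arm.** Under *Intervention group*: "Written consent will be obtained by the PP or another clinic staff member", and this happens before the first prevention visit. These patients may also look at the form online beforehand.
- **Written consent, control arm.** Under *Wait-list control group*, patients are mailed a survey link and "the study consent form to completed and returned to the study team using a pre-addressed, stamped envelope". Their own PP visit comes roughly 12 months later.
- **Written consent is a condition of entry.** Under *Research ethics considerations*: "All patients in the research trial will provide written informed consent".
- **Analysis set.** Under *Outcomes and statistical analysis*, intention-to-treat is taken to mean that "none of the enrolled patients will be excluded from analysis and all patients will be analyzed according to the randomization scheme". The text does not say whether a patient is enrolled at the verbal or the written step.

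**The concern.** In a cluster trial, randomization protects the comparison of patients only if entry to the trial does not depend on the arm. Here the arm is known when patients sign, and what they must do to sign depends on it. One group deals with the PP or clinic staff as a visit approaches. The other returns a form by post with nothing on offer for about a year. The people who drop out between the telephone call and the signature need not be alike in the two arms.

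Analysing every enrolled patient as randomized does not repair this, because the loss happens before enrolment. Patients who never sign supply no data, so no later adjustment can fully recover them. The primary outcome, the proportion of eligible prevention and screening actions achieved, is one on which a patient's motivation is likely to matter. The article does discuss contamination and notes that it would pull the effect towards the null. No comparable reassurance is available for selection at consent.

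**Working it through.** **The plan's own figure.** The concern disputes no number, but the stated total reproduces: 4 cancer survivors + 12 general population patients = 16 per physician; 16 × 1.25 = 20; 20 × 64 physicians = 1280 (64 × 5 = 320 survivors and 64 × 15 = 960 others).

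**Step 1: is the arm known when patients sign?** The milestones list physician randomization second and patient recruitment fourth. A numbered list is not proof of sequence. However, the consent procedure itself differs by arm, so it cannot be carried out unless the allocation is already known.

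**Step 2: the path to enrolment, side by side.**

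| Step | Intervention | Wait-list control |
|---|---|---|
| Invitation and telephone call | common | common |
| Verbal consent | common | common |
| Written consent taken by | PP or clinic staff | post, to the study team |
| When | before the first visit | after agreeing to take part |
| Own PP visit | start of follow-up | about 12 months later |

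Written consent is required of everyone. A patient who agrees by telephone but does not complete the arm's own signing step therefore cannot be in the data. The two sets match up to verbal consent and can diverge after it.

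**Step 3: the follow-up clock.** *Objective* times the primary comparison at 12 months after the initial prevention visit. A wait-list patient has no such visit until the comparison period is over, and an intervention patient who signs but misses the visit has no starting point. The article states no time origin that serves every consented patient.

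**Step 4: how large could the bias be?** The article gives no consent rates, attendance rates or differences in uptake, so this is an illustration under stated assumptions. Let q be the share of prevention-motivated patients in an arm's consented set and d the difference in index between motivated and other patients. With no true effect:

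spurious difference = (q_intervention − q_control) × d

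For an assumed imbalance of 0.10 to 0.30 and an assumed d of 10 to 30 points:

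- lowest: 0.10 × 10 = 1 point
- middle: 0.20 × 20 = 4 points
- highest: 0.30 × 30 = 9 points

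The sign reverses if the control filter is the more selective one.

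**Step 5: what that does to the test.** Taken from *Setting, recruitment, and sample* and *Sample size calculations*: 32 physicians per arm, 20 patients each, ICC 0.30. Assumed: SD of the index 20 to 30 points, and a two-sided 5% test (the article does not state sidedness).

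- Design effect = 1 + 19 × 0.30 = 6.7
- Effective n per arm = 640 / 6.7 = 95.5
- SE = SD × √(2 / 95.5)
- P(reject) = 1 − Φ(1.96 − b/SE) + Φ(−1.96 − b/SE), where b is the spurious difference

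| SD | SE | b = 2 | b = 4 |
|---|---|---|---|
| 20 | 2.89 | 10.6% | 28.2% |
| 25 | 3.62 | 8.6% | 19.8% |
| 30 | 4.34 | 7.5% | 15.1% |

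A 4-point imbalance in either direction would thus raise the nominal 5% error rate to about 15–28%.

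**The case against.** The strongest reply is that the article does not make entry conditional on attending. Consent in the intervention arm is taken before the visit, so a patient can sign, miss the visit and still be enrolled. The RE-AIM section likewise counts agreeing to participate and following through with the visit as separate things. This stands. A reader might infer that the trial compares visit attenders with mail responders. That reader might then reason that, at an assumed 80% or 60% attendance, a 20-point effect in attenders is really 16 (0.8 × 20) or 12 (0.6 × 20) points for the offer, an overstatement of 4 or 8. The documents do not support that: it holds only if signing and attending are the same event.

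Second, returning a form by post is itself a test of motivation and may be the stricter one. This also stands, so a bias in favour of the intervention cannot be assumed.

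Third, choice over whom to invite is limited. All eligible survivors are invited, their status is checked against pathology reports, and general population patients are approached in a random order generated by the study biostatistician. That protects the order of invitation but not who signs afterwards. The sentence "Participating practices may choose to over-sample cancer survivors or patients who meet the definition of complex needs" might be read as letting practices that know the arm shape case mix. It continues by tying the over-sampling to a target of five survivors and 15 others that is the same in both arms, so little of that reading survives; only the share of complex-needs patients is left open.

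Fourth, the timeline, schedule and CONSORT figures are not available here and may define enrolment. A definition there would settle the wording of the analysis set. It would not remove the two consent routes stated in the text.

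**Conclusion.** The concern holds in a limited form. On the article's own text, written consent is compulsory, follows physician randomization and is obtained by a different route in each arm. The enrolled set is therefore formed after allocation by arm-specific filters, and analysing all of it as randomized does not guarantee that the arms are comparable in motivation for prevention.

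Neither the direction nor the size of any bias can be determined from the article. The 1 to 9 points and the 15–28% error rate rest on assumed imbalances, uptake differences and SDs, and show only that a modest imbalance would matter. The conclusion also assumes that enrolment means written consent. The article does not say so in terms, but its ethics section leaves little room for another reading. It does not follow that the intervention arm consists of attenders or that the result would estimate an effect in attenders only. The point merits action because it touches the primary comparison and is cheap to correct before recruitment.

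**What to change.** 1. **One written-consent procedure and time in both arms.** Use the mailed form already planned for controls, returned with the baseline health survey, before any arm-specific scheduling and, where possible, before the patient is told the allocation. Online signing should not be assumed to exist: the article describes only online review of the form, for intervention patients.
2. **Define the primary analysis set** as all patients who consented by that route, whether or not they attend the visit.
3. **Time the 12-month follow-up from a common point** in both arms, such as the date of consent.
4. **Generate each physician's ordered invitation list before the allocation is released to the practice.** The random order is already planned; the addition is its timing.
5. **Report by arm** the numbers invited, verbally agreed, consented and attended.

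**Cost.** A protocol and ethics amendment to the consent sequence, mailing to intervention patients, and some chasing of unreturned forms. The estimated effect may be diluted by consented patients who do not attend, which is the price of estimating the effect of offering the programme.
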